### 7.7 Withdrawal criteria

A subject is free to withdraw from the study at any time. In addition, the Investigator may decide, for reasons of medical prudence, to withdraw a subject. If a subject discontinues study medication dosing, every attempt should be made to keep the subject in the study and continue to perform the required study-related procedures and follow-up procedures. If this is not possible or acceptable to the subject or Investigator, the subject may be withdrawn from the study.

Study medication may also be discontinued in the following instances:

1. If the subject withdraws his/her consent.
2. If the investigator considers in the interest of the subject (i.e. intercurrent illness, unacceptable toxicity) that it is best for them to withdraw their consent.
3. The subject fails to comply with the protocol requirements or fails to cooperate with the investigator.
4. Pregnancy during the course of the study.

The date and reasons for the withdrawal will be clearly stated on the subject's eCRF and source document. Every attempt should be made to arrange follow up visits for subjects who are withdrawn from the trial (including where individuals fall pregnant).

Subjects withdrawing from the trial may be replaced if considered necessary by the Chief Investigator.

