### **9.3 Recording and reporting of AEs, ARs, SAEs, SARs AND SUSARs**

All AEs, ARs, SAEs, SARs and SUSARs will be documented in the eCRF.

The adverse event reporting period will be from consent until the subject's final study visit. In addition, any untoward event that may occur subsequent to the reporting period that the Investigator assesses as possibly, probably or definitely related to the study drug medication will also be reported as an Adverse Reaction.

AEs, ARs, SAEs, , SARs and SUSARs may be directly observed, reported spontaneously by the subject or by questioning the subject at each study visit. These will be followed up until they are resolved or the

subject's participation in the study ends (i.e. until the final eCRF is completed for that subject). In addition, all serious adverse events assessed by the Investigator as possibly related to the investigational medication should continue to be followed even after the subject's participation in the study is over.

Such events should be followed until resolution, or until no further change can reasonably be expected. Deaths occurring more than 30 days after the final dose, which are considered to be unrelated to the study medication, should not be reported as a Serious Adverse Event.

SAEs should be reported immediately to the BSCTU.

All **SAEs** occurring from the time of **consent** until **30** days post cessation of trial treatment must be recorded on the SAE Form and emailed to the BSCTU immediately at [[contact]](mailto:[contact]), at least **within 24 hours** of the research staff becoming aware of the event.

For each **SAE** the following information will be collected:

- full details in medical terms and case description
- event duration (start and end dates, if applicable)
- action taken
- outcome
- seriousness criteria
- causality (i.e. relatedness to trial drug / investigation), in the opinion of the investigator
- whether the event would be considered expected or unexpected in relation to the Reference Safety Information.

Any change of condition or other follow-up information should be emailed to the Sponsor as soon as it is available or at least within 24 hours of the information becoming available. Events will be followed up until the event has resolved or a final outcome has been reached.

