**For SUSARs, defined in section 9.1, the expedited reporting requirement will follow BSCTU SOP.**

## 9.4 Responsibilities

### “Principal Investigator (PI):

Checking for AEs and ARs when participants attend for treatment / follow-up.

1. Using medical judgement in assigning seriousness, causality and expectedness using the Reference Safety Information approved for the trial.
2. Ensuring that all SAEs and SARs (including SUSARs) are recorded and reported to the Sponsor within 24 hours of becoming aware of the event and provide further follow-up information as soon as available. Ensuring that SAEs and SARs (including SUSARs) are chased with Sponsor if a record of receipt is not received within 2 working days of initial reporting.
3. Ensuring that AEs and ARs are recorded and reported to the Sponsor in line with the requirements of the protocol.

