### 9.5 Notification of deaths

All deaths will be reported to the sponsor immediately irrespective of whether the death is related to disease progression, the IMP, or an unrelated event. When recording death, the event or condition that contributed to the fatal outcome will be recorded as a single medical concept, with death as an outcome of that event or condition.

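### Section 9.3 ties the SAE Form window and a death exclusion to stopping trial treatment, which conflicts with Sections 9.1, 9.4 and 9.5 and leaves controls with no defined end point

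*Protocol*

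**What the plan says.** Section 9.3 states the general rule first: "All AEs, ARs, SAEs, SARs and SUSARs will be documented in the eCRF". It then sets the period: "The adverse event reporting period will be from consent until the subject's final study visit". Neither sentence mentions treatment or arm.

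The same section then anchors two rules to treatment:

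- SAEs from consent until 30 "days post cessation of trial treatment must be recorded on the SAE Form", with e-mail to the trials unit within 24 hours.
- "Deaths occurring more than 30 days after the final dose, which are considered to be unrelated to the study medication, should not be reported" as SAEs.

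Other sections bear on this:

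- Section 9.1 defines any untoward occurrence that results in death as an SAE, with no time limit.
- Section 9.4 gives the principal investigator this duty, without a cut-off: "Ensuring that all SAEs and SARs (including SUSARs) are recorded and reported to the Sponsor within 24 hours of becoming aware of the event".
- Section 9.5: "All deaths will be reported to the sponsor immediately irrespective" of cause.
- Section 7.7, on participants who stop study medication: "every attempt should be made to keep the subject in the study and continue to perform the required study-related procedures".
- Table 1, note 16, limits drug dispensing to the maraviroc group, and Section 8.12 lists background therapy as a non-investigational product.

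**The concern.** A safety window in a randomised comparison should run for the same time in both arms and should not depend on staying on drug. Here the form window and the death rule run from an event that only the maraviroc arm can have. In that arm they can close while the participant is still being seen. In the control arm they have no starting point, so a site cannot tell when they end.

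Two practical questions follow. The first is which SAEs reach the trials unit quickly. The unit passes safety information to the oversight committees (Section 9.4), and Appendix 1 gives the DSMB authority to stop the study on a safety signal. The second is whether the same fatal event is an SAE in both arms. An unrelated death at week 80 in someone who stopped maraviroc at week 24 is excluded from the SAE class. The same death in a control, who has no final dose, is not clearly excluded.

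**Working it through.** The protocol states no figure for this point, so there is none to reproduce. The check sets the rules side by side and then illustrates their reach.

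**The rules compared**

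| Rule | Ends at | Defined for controls? |
|---|---|---|
| AE reporting period, with eCRF entry (9.3) | Final study visit | Yes |
| SAE Form and 24-hour e-mail (9.3) | 30 days after trial treatment stops | No clear anchor |
| Unrelated deaths classed as SAEs (9.3) | 30 days after final dose | No clear anchor |
| Investigator reports SAEs to sponsor (9.4) | No limit stated | Yes |
| All deaths notified to sponsor (9.5) | No limit stated | Yes |

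The second and third rows conflict with the others for any participant who stops maraviroc and stays in the study.

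**One participant.** Follow-up is 96 weeks, and 30 days is 30/7 = 4.3 weeks. Weeks outside the form window = 96 − stop week − 4.3, when positive.

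- Stop at week 4: 87.7 weeks
- Stop at week 24: 67.7 weeks
- Stop at week 48: 43.7 weeks
- Stop at week 72: 19.7 weeks

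A participant who completes treatment has a form window to 96 + 4.3 = 100.3 weeks, so nothing before week 96 is missed.

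**The maraviroc arm.** The protocol does not say how many people will stop drug yet remain in follow-up. Assumptions: 30 in the arm (Section 10.1), stopping times uniform over 96 weeks, 10% to 35% stopping drug and all of them followed to week 96. The 35% is the discontinuation benchmark in Section 10.3.2, used only as an upper end.

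- Mean weeks outside per stopper: (96 − 30/7)² / (2 × 96) = 43.8
- Arm follow-up: 30 × 96 = 2,880 weeks
- 10% (3 people): 3 × 43.8 / 2,880 = 4.6%
- 35% (10.5 people): 10.5 × 43.8 / 2,880 = 16.0%

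**Expected events.** Assume a constant hazard h = −ln(1 − p)/96 for a 96-week SAE risk p. At p = 10%, the full arm expects 2,880 × h = 3.16 events. Those outside the form window number 0.14 (10% stopping) to 0.50 (35% stopping). At p = 5% the range is 0.07 to 0.25, and at p = 20% it is 0.31 to 1.07.

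**Under the eCRF period.** Consent to final visit leaves 0 weeks uncovered before week 96 in either arm.

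**The case against.** The strongest reply is that the 30-day clause limits a form and an e-mail, not the recording of SAEs. Section 9.3 puts every SAE in the eCRF, Section 9.4 has safety data collected centrally on the trial database, and the DSMB is to review overall safety data. Nothing says that SAE Forms feed the between-arm counts. This stands, and it rules out two stronger readings.

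- A reader might infer that serious-event counts will be non-comparable, or that the maraviroc arm will be under-counted. The documents do not support that. Counts from the eCRF cover the same period in both arms. With no defined control window, a direction of bias cannot be shown.
- A reader might infer that the primary measure is biased. It is not. That measure is the proportion reporting adverse events (Section 3.3), an SAE after stopping maraviroc still counts as an adverse event, and no SAE-count endpoint is stated.

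It is also tempting to use the 33% attrition in Section 10.1 as the number of stoppers: 10 × 43.8 / 2,880 = 15.2%. That figure describes people lost from the analysis, not people who stop drug and stay. Section 8.11 says that compliance below 80% will probably lead to withdrawal from the study, which shrinks the relevant group further.

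On deaths, Sections 9.3 and 9.5 can be read together: notify every death, but do not class some of them as SAEs. Deaths are then not lost. On serious reactions, Section 9.9 keeps SUSAR reporting open however long after dosing.

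The eCRF answer does not settle everything. The death sentence concerns classification rather than paperwork, and it departs from the SAE definition in Section 9.1. It cannot be confined to the time after the study, because it runs from the final dose and not the final visit. The form is also the stated route for rapid reporting, and for that route Sections 9.3 and 9.4 give sites different instructions.

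**Conclusion.** The inconsistency is real and should be corrected. Section 9.3 contradicts itself and Sections 9.1, 9.4 and 9.5 on when SAE and death reporting ends, and two of its rules have no anchor in the control arm. What can differ by arm is expedited SAE reporting, any DSMB tally built from SAE Forms, and whether a late unrelated death is an SAE.

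The quantitative effect is probably small. About 5% to 16% of maraviroc-arm follow-up would lie outside the form window, or half an expected event at most for a 10% SAE risk. It reaches about one event only at a 20% risk with 35% stopping. These figures rest entirely on the assumed share of stoppers who remain, uniform stopping times and the assumed SAE risk, none of which the protocol supplies. The case for correction rests on the contradictory instructions to sites, which an analysis plan cannot repair afterwards.

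**What to change.** Reconcile Sections 9.3, 9.4 and 9.5 around one SAE and death reporting window for both arms that does not depend on staying on drug:

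- Use at least the existing period from consent to the final study visit, extended to 30 days after the last maraviroc dose where that is later.
- Apply the exclusion of late unrelated deaths only outside that window, so that it agrees with the definition in Section 9.1.
- State that SAE and death counts by arm, including those for the DSMB, come from the eCRF over that period.

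The cost is a protocol wording change and a few more SAE Forms for people who stop maraviroc early. Those events are already due in the eCRF, so no new visits or data items are needed.

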**For SUSARs, defined in section 9.1, the expedited reporting requirement will follow BSCTU SOP.**

## 9.4 Responsibilities

### “Principal Investigator (PI):

Checking for AEs and ARs when participants attend for treatment / follow-up.

1. Using medical judgement in assigning seriousness, causality and expectedness using the Reference Safety Information approved for the trial.
2. Ensuring that all SAEs and SARs (including SUSARs) are recorded and reported to the Sponsor within 24 hours of becoming aware of the event and provide further follow-up information as soon as available. Ensuring that SAEs and SARs (including SUSARs) are chased with Sponsor if a record of receipt is not received within 2 working days of initial reporting.
3. Ensuring that AEs and ARs are recorded and reported to the Sponsor in line with the requirements of the protocol.

**Chief Investigator (CI) / delegate or independent clinical reviewer:**

1. Clinical oversight of the safety of patients participating in the trial, including an ongoing review of the risk / benefit.
2. Using medical judgement in assigning seriousness, causality and expectedness of SAEs where it has not been possible to obtain local medical assessment.
3. Using medical judgement in assigning expectedness
4. Immediate review of all SUSARs.
5. Review of SAEs and SARs in accordance with the trial risk assessment and protocol as detailed in the Trial Monitoring Plan.
6. Assigning Medical Dictionary for Regulatory Activities (MedDRA) or Body System coding to all SAEs and SARs.
7. Preparing the clinical sections and final sign off of the Development Safety Update Report (DSUR).

**Sponsor (as delegated to BSCTU):**

1. Central data collection and verification of AEs, ARs, SAEs, SARs and SUSARs according to the trial protocol onto a MACRO database.
2. Reporting safety information to the CI, delegate or independent clinical reviewer for the ongoing assessment of the risk / benefit according to the Trial Monitoring Plan.
3. Reporting safety information to the independent oversight committees identified for the trial (Data Safety and Monitoring Board(DSMB) and / or Trial Steering Committee (TSC)) according to the Trial Monitoring Plan.
4. Expedited reporting of SUSARs to the Competent Authority (MHRA in UK) and REC within required timelines.
5. Notifying Investigators of SUSARs that occur within the trial.
6. Checking for (annually) and notifying PIs of updates to the Reference Safety Information for the trial.
7. Preparing standard tables and other relevant information for the DSUR in collaboration with the CI and ensuring timely submission to the MHRA and REC.

The role of the Trial Steering Committee (TSC) is to provide overall supervision for the HEPMARC trial on behalf of the Trial Sponsor and the Trial Funder and to ensure that the trial is conducted according to the guidelines for Good Clinical Practice (GCP), Research Governance Framework for Health and Social Care and all relevant regulations and local policies.

**Data Safety and Monitoring Board (DSMB):**

In accordance with the Trial Terms of Reference for the DSMB, periodically reviewing overall safety data to determine patterns and trends of events, or to identify safety issues, which would not be apparent on an individual case basis.

### 9.5 Notification of deaths

All deaths will be reported to the sponsor immediately irrespective of whether the death is related to disease progression, the IMP, or an unrelated event. When recording death, the event or condition that contributed to the fatal outcome will be recorded as a single medical concept, with death as an outcome of that event or condition.

### 9.6 Pregnancy reporting

- All pregnancies within the trial (either the trial participant or the participant's partner) will be reported to the BSCTU using the relevant Pregnancy Reporting Form within 24 hours of notification
- Pregnancy will not be considered an AE unless a negative or consequential outcome is recorded for the mother or child/foetus. If the outcome meets the serious criteria, this will be considered an SAE.
- Pregnancy subjects will be followed up by the HIV pregnancy service of the relevant site and reported to the antiretroviral pregnancy registry.

### 9.7 Overdose

- Overdoses will be reported to the sponsor immediately and this information will be placed on the deviation log)
- Overdose will be observed from patient comments.
- An overdose will constitute more than 1200mg of maraviroc per day
- There is no specific antidote for overdose with maraviroc. Treatment of overdose will depend on the amount of overdose and should consist of general supportive measures which may include keeping the patient in a supine position, careful assessment of patient vital signs, blood pressure and ECG. If indicated, elimination of unabsorbed active maraviroc should be achieved by emesis or gastric lavage. Administration of activated charcoal may also be used to aid in removal of unabsorbed active substance. Since maraviroc is moderately protein bound, dialysis may be beneficial in removal of this medicine. Further management will be as recommended by the national poisons centre.
- If an SAE is associated with the overdose, the overdose will be fully described in the SAE report form.

### 9.8 Reporting urgent safety measures

If any urgent safety measures are taken the CI/Sponsor shall immediately and in any event no later than 3 days from the date the measures are taken, give written notice to the MHRA and the relevant REC of the measures taken and the circumstances giving rise to those measures.

### **9.9 The type and duration of the follow-up of subjects after adverse events.**

The type and duration of follow up of subjects after adverse events will depend on the seriousness of the event and the specific nature of the event to be determined at the discretion of the chief investigator.

Any SUSAR related to the IMP will need to be reported to the Sponsor irrespective of how long after IMP administration the reaction has occurred.

### **9.10 Development safety update reports**

The BSCTU will submit DSURs once a year throughout the clinical trial, or on request to the Competent Authority (MHRA in the UK), Ethics Committee and NHS Trusts.

## **10 STATISTICS AND DATA ANALYSIS**

### **10.1 Sample size calculation**

This is a pilot study to evaluate the feasibility and potential efficacy of addition of maraviroc to optimised background combination antiretroviral therapy and therefore no formal sample size calculation has been conducted. Results may be used to estimate the variability of the treatment effect of MVC on the ELF score which in turn may inform the sample size calculation for a larger placebo-controlled RCT.

In a previous biopsy study, a unit increase of 1 in the ELF score was associated with a 2.5-fold increased risk of a liver-related event (adjusted for age and stage of fibrosis) and therefore a unit increase of 1 is deemed to represent a clinically important entity [24]. Assuming the SD of the ELF score is 1.12, with 20 patients in each group for the analysis, a difference in ELF of 1 point can be estimated with a 95% confidence interval from 0.6 to 1.4. Assuming an attrition rate of 33%, a target of 30 individuals will be recruited per group [23].

A t-method will be used to estimate the difference in ELF scores, together with 95% confidence intervals, between the two groups. P-values will not be presented.

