### **7.3 The randomisation scheme**

After written informed consent has been received and eligibility established, subjects will be randomised 1:1 into the maraviroc and non-maraviroc groups (Groups A and B respectively) at the baseline visit (day 1). In addition, there will be stratification according to (1) current exposure or past history of  $\geq 6$  months exposure to protease inhibitor (PI)-containing antiretroviral therapy versus no current exposure and less than 6 months past exposure to PI-containing therapy and (2) BMI  $\geq 25$  versus  $< 25$  and (3) current exposure to a lipid-lowering agent and (4) being diabetic type 1 or 2 vs non-diabetic.

The rationale for this stratification is to attempt to reduce the potential for imbalance in factors considered a priori to be prognostic of ELF. Elevated BMI may be associated with faster progression of hepatic fibrosis in NAFLD patients. In addition, exposure to PI-containing therapy has in some studies been associated with accelerated fibrosis progression [1]. In other studies, lipid-lower therapies may reduce fibrosis progression [22]. Finally, diabetes mellitus has been identified as one of the strongest predictors of fibrosis progression in NAFLD patients [2].

The web-based Sealed Envelope™ system will be used to allocate individuals randomly to the maraviroc or non-maraviroc groups. The statistician will provide the randomisation list. The HEPMARc Randomisation Guide should be followed by the study team.

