### 10.3.3 Secondary outcome analysis

The analysis of the following secondary outcomes will be presented as the estimated difference and 95% confidence interval between groups using a t-method from baseline to 48 and 96 weeks.

The mean change in ELF score

Mean change in the Fibroscan stiffness

Mean change in Fibroscan CAP score

Mean change in fasting lipids (HDL:cholesterol ratio, HDL, LDL, TG), ALT, fasting glucose, HbA1c, in the maraviroc and non-maraviroc groups

Mean change in the BMI, waist circumference and weight

Mean change in the CD4 count

Mean scores for the CLDQ:NAFLD , SF-36 and WAIP:SAH questionnaires

Differences in the following measures from baseline to 48 and 96 weeks will be presented exact 95% binomial confidence intervals:

% with HIV viral load not detected (48 and 96 weeks)

% with CT liver:spleen attenuation ratio <1.0 (96 weeks only)

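### The 95% CI of 0.6 to 1.4 given in Section 10.1 for a 1-point ELF difference does not follow from its own inputs, which give about 0.28 to 1.72

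*Protocol*

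**What the plan says.** Protocol Section 10.1 disclaims a formal sample size calculation and offers a precision statement instead. Its inputs are "Assuming the SD of the ELF score is 1.12" and "with 20 patients in each group for the analysis". From these it concludes that "a difference in ELF of 1 point can be estimated with a 95% confidence interval from 0.6 to 1.4".

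The method is named in the same section: "A t-method will be used to estimate the difference in ELF scores, together with 95% confidence intervals, between the two groups". Allocation is equal: under Section 7.3, "subjects will be randomised 1:1 into the maraviroc and non-maraviroc groups". The recruitment target follows from the analysed number: "Assuming an attrition rate of 33%, a target of 30 individuals will be recruited per group".

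Section 10.3.3 plans the ELF comparison on mean change, reported as the "estimated difference and 95% confidence interval between groups using a t-method from baseline to 48 and 96 weeks". The protocol gives no SD of change and no correlation between baseline and follow-up.

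**The concern.** An SD of 1.12 with 20 patients per group looks too imprecise for a between-group difference to be known to within 0.4. This is the only precision figure in the protocol, and it leads directly into the target of 30 per group. Section 10.1 also treats 1 ELF point as clinically important and rules out p-values, so the ELF result will be read through its confidence interval. If the printed width is wrong, readers of the protocol are misinformed about how closely 60 participants can locate an effect of that size.

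The basis of the SD is a related question. Section 10.1 speaks of the SD of the score, while Section 10.3.3 analyses change in the score.

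**Working it through.** **Inputs.** SD 1.12, n = 20 analysed per group, difference 1 point, 95% confidence and a t-method between two groups (all Section 10.1); 1:1 allocation (Section 7.3).

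**The plan's figure.** Limits of 0.6 and 1.4 imply a half-width of (1.4 − 0.6)/2 = 0.4.

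**Recalculation.** For two independent means with a common SD, the half-width is q × SD × √(2/n).

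- Standard error: 1.12 × √(2/20) = 0.354.
- By t on 38 degrees of freedom: 2.024 × 0.354 = 0.717, giving 0.28 to 1.72.
- By the normal quantile: 1.960 × 0.354 = 0.694, giving 0.31 to 1.69.
- Ratio to the printed half-width: 0.717/0.4 = 1.8.
- Confidence level of ±0.4 at 20 per group: about 73%.

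**Attempts to reproduce 0.4.**

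| Reading | Half-width |
|---|---|
| 20 per group, 90% interval (t) | 0.597 |
| 20 per group, 80% interval (t) | 0.462 |
| 20 per group, one standard error | 0.354 |
| 20 per group, 1.12 read as a variance (t) | 0.677 |
| 20 per group, SD divided by √2 (t) | 0.507 |
| 30 per group, no attrition (t) | 0.579 (0.42 to 1.58) |
| 40 per group (t) | 0.499 |
| 60 per group (normal / t) | 0.401 / 0.405 |
| Mean of one group, n = 30 (normal / t) | 0.401 / 0.418 |

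Only the last two rows come close, and neither uses the inputs that Section 10.1 states.

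**What 0.4 would require.** At SD 1.12, the smallest number per group with a t half-width of 0.40 or less is 62. If the limits were rounded to one decimal, the half-width could be as large as 0.45, which still needs 49 per group. At 20 per group, the SD would have to be 0.4/(2.024 × √(2/20)) = 0.625, or 0.70 with the rounding allowance.

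**Change scores.** If the variance is the same at both visits, the SD of change is 1.12 × √(2(1 − r)), where r is the correlation between baseline and follow-up. The document gives no r, so the values below are assumptions (20 per group, t-method).

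| Assumed r | SD of change | Half-width |
|---|---|---|
| 0.5 | 1.12 | 0.72 |
| 0.7 | 0.868 | 0.56 |
| 0.8 | 0.708 | 0.45 |
| 0.9 | 0.501 | 0.32 |

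Setting the SD of change to 0.625 gives r = 1 − 0.625²/(2 × 1.12²) = 0.84.

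**Attrition.** 20/(1 − 0.33) = 29.9, so 30 per group is correct.

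**The case against.** The strongest defence is that little depends on this sentence. The primary objective and all primary endpoints concern feasibility and acceptability, and ELF is secondary. The protocol does not derive 20 per group from a target width, and no decision rule uses the interval. A later trial would draw on the variability observed in this pilot, and the final report would carry the interval actually obtained. All of this stands and limits the importance of the error, but it does not make the printed interval right.

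A second defence is that the planned analysis uses change scores, which could be less variable than single scores. A half-width of 0.4 is attainable that way, but only with a correlation of about 0.84 (about 0.80 with the rounding allowance). Section 10.1 describes 1.12 as the SD of the score and claims no such correlation, so this defence supplies an assumption that the text does not make.

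Four stronger readings are tempting and are not supported:

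- A reader might infer that the corrected interval nearly reaches zero. Its lower limit is 0.28, and an estimate of 1 lies 1/0.354 = 2.8 standard errors from zero.
- A reader might judge the interval by whether it separates 1 point from half a point. The protocol sets no such benchmark; the only ELF difference it calls important is 1.
- A reader might conclude that the authors used a one-group formula with n = 30. The figure fits, but 1.12/√30 is algebraically the same as 1.12 × √(2/60), so entering the total of 60 as a per-group number gives the same 0.401. The documents do not show which slip occurred, if either.
- A reader might say that the SD of change must differ from 1.12. With equal variances it equals 1.12 at r = 0.5 and can be larger or smaller otherwise. The fair point is only that Section 10.1 does not relate its SD to the planned analysis.

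**Conclusion.** The printed interval is wrong as written. On the section's own inputs and method, a 1-point difference would carry a 95% CI of about 0.28 to 1.72, so the half-width is 0.72 where the text implies 0.4. This assumes only a common SD of 1.12 in both groups and 20 analysed in each. Neither the choice of quantile, nor the absence of attrition, nor rounding closes the gap.

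The error overstates what the pilot can say about the size of an ELF effect. It does not undermine the feasibility objectives or the target of 60, and it does not mean that a 1-point difference would be indistinguishable from none. How wide the interval will be in practice depends on the SD of change, which the protocol does not give.

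**What to change.** In Section 10.1, restate the interval: with 20 per group and an SD of 1.12, a 1-point difference would be estimated with a 95% CI from about 0.28 to 1.72. Leave the recruitment target and the attrition step unchanged.

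In the same place, say whether 1.12 is the SD of the ELF score or of the change that Section 10.3.3 analyses. If a narrower interval is claimed because change scores are used, state the assumed correlation and give the matching half-width for the planned change-score t-method: about 0.72, 0.56 or 0.45 at correlations of 0.5, 0.7 or 0.8. Figures for a baseline-adjusted covariance analysis should not be substituted, because Section 10.3.3 does not plan one.

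The cost is one corrected sentence and one clarification. Trial conduct does not change; the stated precision becomes less favourable.
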